### Quality control measures

#### Monitoring

Continuous central and on-site monitoring of the study is performed by the Clinical Trial Unit for quality control and assurance purposes; to evaluate the progress of the study; to verify the accuracy and completeness of case report forms (CRFs) ; to ensure that all protocol requirements are met, and all applicable local authority regulations and investigator’s obligations are being fulfilled; and to resolve any inconsistency in the study records. Monitoring will consist of one initiation visit (12 hours), two monitoring visits (two days each) per year and one close-out visit (12 hours) each per center.

### Sample size considerations and statistical analyses

#### Sample size consideration

We base our sample size consideration on the planned 1:1 ratio between the two groups of patients (SAP administered 75 to 30 minutes (arm A) versus less than 30 minutes to 0 minutes (arm B) before surgery), according to the results of our observational study conducted in the years 2000 to 2001 at the University Hospital of Basel [62]. In this study, an average SSI rate of 4.7% in 3,836 general, oncologic, vascular and orthopedic trauma surgery procedures was observed. This rate varied between 4.7% and 6.8% with SAP given between 29 and 0 minutes before incision, and between 2.4% and 3.4% with SAP given 75 to 30 minutes prior to incision. The main scenario for sample size calculations was that administration of SAP 75 to 30 minutes before surgery (in the anesthesia room) will result in a 33% relative reduction of SSI risk and that SAP administration less than 30 minutes before surgery (in the operating room) will result in a SSI rate of 5%. We therefore plan to randomize 5,000 patients in a 1:1 ratio, thus resulting in two groups of 2,500 patients each. Sample size calculations were conducted using the ‘sampsi’ command of Stata Software Version 11 with a power of 80% and a two-sided type I error of 5%.

#### Statistical analyses

In order to analyze the difference in SSI occurrence between the two timing groups, logistic regression models will be used with the treatment group as the main exposure variable. The main analysis will be an intention-to-treat analysis. In secondary analyses, the logistic regression model will include the following known and suspected baseline risk factors for SSI: wound classification, ASA score, NNIS score, age, body mass index categories, presence of diabetes, smoking status, adherence to aseptic technique, and experience of the surgical team.

Additional analyses of the study will assess whether the difference of SSI risk in the two timing groups differ in specific subsets of patients: age (≥65 versus <65 years), body mass index (≥30 versus <30 kg/m^2^), diabetes (with versus without), and previous or current smoker (yes versus no). The rationale for these analyses is that we suspect the pharmacokinetics of the study drugs to be different in these subgroups. This might have an impact on the efficacy of SAP in the relevant timing categories.

Descriptive analyses will show the difference in the distribution of exact timing by randomization group and further analyses will focus on the detailed association of the exact timing of SAP with SSI risk. These latter analyses will be of observational character.

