## Methods/Design

### Study design and sites

This bi-center prospective RCT is being conducted at the University Hospital of Basel and the Hospital of Aarau, two tertiary referral centers in Switzerland. The trial has been registered on ClinicalTrials.gov under the identifier NCT01790529*.*

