### Randomization and intervention

After written informed consent is obtained from eligible patients, they are randomized electronically and stratified by hospital, according to pre-existing randomization lists. Randomization results are presented both electronically and printed to the anesthesiologist responsible for SAP administration. Patients are randomized in a 1:1 ratio to have SAP administered in the anesthesia room, which is located next to the actual operating room (arm A), versus in the operating room itself (arm B). Patients in arm A receive the antibiotics between arrival in the anesthesia room and transfer to the operating room, corresponding to the time window of 75 to 30 minutes before the scheduled incision. Patients in arm B receive the antibiotics between arrival in the operating room and the time of incision, corresponding to the time window of less than 30 minutes to 0 minutes before the scheduled incision, preferably as close to the incision time as possible. SAP is administered by the anesthetic team to all patients via single-shot, intravenous infusion of 1.5 g or 3 g for patients ≥80 kg of cefuroxime in 100 ml of a 0.9% sodium chloride solution within 5 minutes and is combined with metronidazole (500 mg or 1,000 mg for patients ≥80 kg intravenous infusion, within 5 minutes) in colorectal patients, who receive no additional intraluminal antibiotics. Hence, the duration of the infusion is highly standardized. The anesthesiologist or anesthetic nurse who administers SAP records the exact time at which the infusion starts. Until 29 April 2013, corresponding to the inclusion of the first 221 patients, we instead recorded the time that the infusion ended. We had to make this amendment for feasibility reasons after consulting several opinion leaders in the field and the corresponding literature, and confirming that the standard in the US is to report when the infusion starts. In operations that last more than four hours, SAP is re-administered every four hours after the first dose according to clinical standards. In patients with impaired renal function, this re-dose will be adapted according to the creatinine clearance.

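### Randomization is stratified by hospital, but the main logistic model names only treatment and the nine-variable adjusted model omits hospital: a minor mismatch that one model term would repair

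*Protocol article*

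**What the plan says.** On design, the article states under Study design and sites: "This bi-center prospective RCT is being conducted at the University Hospital of Basel and the Hospital of Aarau". Under Randomization and intervention it says of consenting patients that "they are randomized electronically and stratified by hospital, according to pre-existing randomization lists". Hospital is the only stratification factor mentioned.

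On analysis, the Statistical analyses section says that "logistic regression models will be used with the treatment group as the main exposure variable", and then: "The main analysis will be an intention-to-treat analysis". Covariates first appear in the next sentence: "In secondary analyses, the logistic regression model will include the following known and suspected baseline risk factors for SSI". The list is wound classification, followed by "ASA score, NNIS score, age, body mass index categories, presence of diabetes, smoking status, adherence to aseptic technique, and experience of the surgical team". That makes nine variables, and hospital is not among them.

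Hospital is also absent from the subgroup paragraph and from the Interim analysis section. Nowhere does the article say that an analysis is adjusted for, or stratified by, hospital.

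**The concern.** When allocation is balanced within strata, the matching analysis conditions on those strata. Here the adjusted model goes down to the experience of the surgical team, yet leaves out the one factor that was balanced by design.

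Hospital could plausibly carry information about the outcome. The planning rates come from Basel alone (Sample size consideration), and no infection rate is given for Aarau. Infections are first registered by ward staff at each site (Study endpoints). If the two hospitals differ in infection risk, an analysis without hospital forgoes a little power, and its odds ratio is a marginal one and not the within-hospital one.

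What is at stake is agreement between design and analysis, and a small amount of power. The validity of the trial is not in question.

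**Working it through.** **Inputs from the article.** Arm B infection rate 5%; relative reduction 33%, so arm A 5% × 0.67 = 3.35%; 2,500 per arm; two-sided 5%; 80% power; final significance level 4.5% (Interim analysis). Recruitment to 18 February 2014 was 1,492 at Basel and 609 at Aarau (Trial status), so the Basel share is 1,492/2,101 = 71%.

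**Assumed.** The between-hospital ratio of infection rates is not given; a range of 1 to 3 is used.

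**Step 1: the plan's own sample size.** With p1 = 0.05, p2 = 0.0335 and mean 0.04175, the two-proportion formula is

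n = [1.96·√(2·0.04175·0.95825) + 0.842·√(0.05·0.95 + 0.0335·0.9665)]² / 0.0165² ≈ 2,306 per arm.

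With the continuity correction, n/4·[1 + √(1 + 4/(n·0.0165))]² ≈ 2,426 per arm, or 4,852 in total. This agrees with the planned 2,500 per arm to within 3%, taking the correction as what the software applied.

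**Step 2: error rate and power with and without hospital.** There were 200,000 simulated trials per scenario, with arms balanced exactly within hospital and an overall arm B rate of 5%. The unadjusted score test was compared with the hospital-stratified score test, which is the score test of a logistic model with treatment and hospital. Results at a Basel share of 71%, each cell without / with hospital, in %:

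| Rate ratio | Type I, nominal 5% | Type I, nominal 4.5% | Power, 5% level | Power, 4.5% level |
|---|---|---|---|---|
| 1 | 5.09 / 5.09 | 4.54 / 4.54 | 83.39 / 83.39 | 82.15 / 82.16 |
| 1.5 | 5.00 / 5.01 | 4.47 / 4.48 | 83.43 / 83.44 | 82.23 / 82.33 |
| 2 | 4.92 / 4.98 | 4.40 / 4.47 | 83.57 / 83.68 | 82.37 / 82.58 |
| 3 | 4.89 / 5.05 | 4.37 / 4.57 | 83.37 / 83.71 | 82.11 / 82.57 |

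The Monte Carlo standard error of a type I error near 5% is √(0.05·0.95/200,000) ≈ 0.05 points. The largest power difference is 82.57 − 82.11 = 0.46 points. At a 50% share and ratio 3, power at the 4.5% level is 82.30 / 82.64, a difference of 0.34 points.

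**Step 3: the odds ratio itself.** The within-hospital odds ratio is (0.0335/0.9665)/(0.05/0.95) = 0.6586, with logarithm −0.4177. Per arm, take 0.71 × 2,500 = 1,775 patients at Basel and 725 at Aarau.

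- Without hospital: pool the rates over hospitals, then SE = √[1/(2,500·pB(1−pB)) + 1/(2,500·pA(1−pA))].
- With hospital: Vh = 1/(nh·pBh(1−pBh)) + 1/(nh·pAh(1−pAh)) in each hospital, then SE = 1/√(ΣVh⁻¹).

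| Assumed arm B rates, Basel v Aarau | Pooled arm B, arm A | Odds ratio without / with | SE without / with | Absolute z without / with |
|---|---|---|---|---|
| 4% v 6% | 4.58%, 3.07% | 0.6590 / 0.6586 | 0.1504 / 0.1505 | 2.773 / 2.776 |
| 3% v 7% | 4.16%, 2.79% | 0.6605 / 0.6586 | 0.1575 / 0.1580 | 2.634 / 2.644 |

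Adding hospital raises the standard error of the log odds ratio very slightly and moves the estimate slightly further from 1. The net gain in the test statistic is about 0.003 to 0.01.

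**The case against.** **The main model may already contain hospital.** Calling treatment the main exposure variable does not exclude a stratification term, and whether a primary model carries one is often left to a full protocol or analysis plan that is not shown here. This stands as a limit: for the main model the omission is a reading, supported by covariates being introduced only for the secondary analyses. It does not reach the adjusted model, whose covariates are listed one by one.

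**The hospitals may not differ.** No infection rate by hospital is given. The article describes one surveillance process for both sites, with a standardized questionnaire and blinded specialist validation. Aarau's later start cannot confound the comparison, since allocation is 1:1 within each hospital. This also stands, and with equal rates the two analyses coincide.

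**The change has consequences elsewhere.** The overall type I error of 4.9% was simulated with a single 5% risk in both arms, so a new primary model must carry through to the interim rule. This is correct and belongs in the fix.

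**Stronger readings are tempting, and the figures do not support them.** A reader might infer that the P-value is unreliable against the 4.5% level; the simulated type I error without hospital is about 4.4% to 4.5% there, so nothing is inflated. A reader might also infer that between-hospital variation sits in an error term and overstates the standard error. A logistic model has no residual error term. The variance argument p(1−p)/Σwh·ph(1−ph) − 1, which gives 0.19% for 4% v 6% and 0.83% for 3% v 7%, concerns a risk difference. On the log odds ratio scale, the standard error without hospital is marginally the smaller one.

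**Conclusion.** The mismatch is real but minor. It is explicit for the adjusted model and the natural reading for the main model.

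The unadjusted test remains valid and at most slightly conservative: type I error is about 4.9% at nominal 5% if the hospitals' rates differ threefold. Power lost is at most about 0.5 points over rate ratios of 1 to 3 and Basel shares of 50% or 71%, and zero if rates are equal. The shift of the odds ratio toward 1, from 0.6586 to 0.6590 or 0.6605 in the two cases worked, is non-collapsibility: the marginal and within-hospital odds ratios are different quantities.

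These sizes rest on assumed between-hospital rates and, for the 71% share, on the recruitment split of February 2014. Sample size and interpretation of the trial are unaffected.

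**What to change.** Add hospital (Basel v Aarau) as a fixed effect to the main intention-to-treat logistic model and to the adjusted model. Prespecify the hospital-adjusted treatment effect as the primary test, before any outcome data by arm are seen. Use the same model for the interim predictive-probability calculation, and rerun the type I error simulation with it so that the stated 4.9% refers to the test actually used.

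The cost is one parameter, a sentence in the Statistical analyses section and one rerun of the simulation. The target becomes the within-hospital odds ratio, which should be said. The sample size stays at 5,000.

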### Patient and procedure characteristics

The selection of demographics and assessment of patients’ health profiles are in accordance with the design used in our observational study [62], including all relevant patient characteristics, as well as preoperative laboratory values and factors that might influence wound healing. These involve, but are not limited to, American Society of Anesthesiologists (ASA) score, number of comorbidities on admission, smoking status, diabetes mellitus, immunosuppressive drugs, body mass index, preoperative albumin, wound class, type and duration of surgery, experience of the surgical team, surgical specialty, intraoperative core temperature, adherence to aseptic technique, and emergency procedure. The Study on the Efficacy of Nosocomial Infection Control and the National Nosocomial Infections Surveillance System (NNIS) SSI risk indices are based on some of these variables and will be calculated for each patient.

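### The primary logistic test leaves out preoperative risk factors and the stratification factor; adjusting for them would be a valid, modest gain in power (about 0 to 3 points), not the correction of an error

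*Protocol article*

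**What the plan says.** All references are to the protocol article.

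- **Main analysis.** Under Statistical analyses, "logistic regression models will be used with the treatment group as the main exposure variable", and "The main analysis will be an intention-to-treat analysis". No covariate is named for this model.
- **Covariates.** They enter afterwards: "In secondary analyses, the logistic regression model will include the following known and suspected baseline risk factors for SSI". The list is "wound classification, ASA score, NNIS score, age, body mass index categories, presence of diabetes, smoking status, adherence to aseptic technique, and experience of the surgical" (the last item being how experienced the operating team is).
- **Data.** Patient and procedure characteristics describes the recorded variables as "including all relevant patient characteristics, as well as preoperative laboratory values and factors that might influence wound healing". Of the two SSI risk indices it says "SSI risk indices are based on some of these variables and will be calculated for each patient". Archiving and data retention adds that only the randomisation result and the follow-up status are acquired purely for the study, so the covariates are routine source data.
- **Stratification.** Under Randomization and intervention, patients are handled so that "they are randomized electronically and stratified by hospital". Hospital is named in neither the main nor the secondary model.
- **Sample size.** The calculation assumes "SAP administration less than 30 minutes before surgery (in the operating room) will result in a SSI rate of 5" per cent, a 33% relative reduction in the other arm and 2,500 patients per arm, with Stata's sampsi command, 80% power and two-sided 5%. The Interim analysis section requires P<4.5% at the end.

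The article never calls the main model unadjusted. That is the natural reading of the contrast with the secondary analyses.

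**The concern.** The trial pools clean, clean-contaminated and contaminated procedures from general, oncologic, vascular and orthopedic trauma surgery, so baseline risk of SSI is likely to vary between patients. In a randomised trial, a logistic model that adjusts for prognostic baseline variables gives a treatment test with at least about the same power as the unadjusted one, and it keeps the type I error. The article plans to hold such variables, itself calls them known or suspected risk factors, and gives no reason for keeping them out of the confirmatory test.

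What is at stake is some unused power. The choice has to be fixed in advance, because an adjusted primary analysis chosen after the results are seen would not be credible.

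**Working it through.** **1. Reproduce the plan's own figure.** Inputs from Sample size consideration: p1 = 0.05; p2 = 0.05 × (1 − 0.33) = 0.0335; d = 0.0165; mean risk 0.04175; two-sided 5%; power 80%.

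n per arm = [1.96·√(2·0.04175·0.95825) + 0.8416·√(0.05·0.95 + 0.0335·0.9665)]² / 0.0165² = 2,306.

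With the continuity correction that sampsi applies by default, n = 2,426 per arm, or 4,852 in total. The plan's 5,000 is within 3% of this and is therefore reproduced as an unadjusted two-proportion design.

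**2. Unadjusted power at 2,500 per arm.** SE0 = √(2·0.04175·0.95825/2,500) = 0.005657. SE1 = √[(0.0475 + 0.03238)/2,500] = 0.005652. Power = Φ[(d − z·SE0)/SE1].

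- At 5% (z = 1.960): Φ(0.957) = 83.1%. With the continuity correction it is 81.2%.
- At the final 4.5% criterion (z = 2.005): Φ(0.913) = 81.9%. With the continuity correction it is 80.0%.
- At 4.5% with 5% of outcomes missing (an assumption; 2,375 per arm): 79.9%.

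**3. Power with adjustment.** The documents give no prognostic strength, so it is varied. Each patient has a standard normal risk score x, and logit P(SSI) = a + s·x. The intercept a is set in each arm so that the marginal risks stay at 5% and 3.35%. Each simulated trial of 2 × 2,500 patients is analysed by the Wald test with and without x, in 14,000 runs per scenario.

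| s | AUC | 4.5%: unadjusted → adjusted | 5%: unadjusted → adjusted |
|---|---|---|---|
| 0.75 | about 0.70 | 81.8% → 82.9% | 82.8% → 83.8% |
| 1.00 | about 0.76 | 82.2% → 84.1% | 83.3% → 85.2% |
| 1.25 | about 0.80 | 81.9% → 85.0% | 83.0% → 86.1% |

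The gains are about 1, 2 and 3 points. The Monte Carlo standard error of one power figure is √(0.82·0.18/14,000) = 0.3 points.

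**4. Weaker covariates.** A 4,000-run simulation at AUC about 0.64 gave a gain of at most 0.3 points. A further simulation with eight estimated covariates (3,000 trials per scenario, P<4.5%) gave gains of 0.7, 0.2, 0.4, 1.4 and 1.6 points at AUC 0.60, 0.64, 0.68, 0.71 and 0.75. With a standard error near √(0.82·0.18/3,000) = 0.7 points for each power figure, the first three should be read only as small. The gain is below 1 point unless the AUC reaches about 0.7.

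**5. Patient equivalents.** If adjustment multiplies the mean test statistic by k, it is worth 5,000·(1 − 1/k²) patients. The simulated ratios 1.014, 1.026 and 1.045 give 137, 250 and 421, or roughly 140 to 420 for AUC 0.70 to 0.80.

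**6. Type I error.** With 5% risk in both arms and AUC about 0.76 (14,000 runs), rejection at the 5% level was 5.2% both without and with adjustment. At 4.5% it was 4.7% for both. This check does not include the interim rule.

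**The case against.** The strongest case against is that nothing here is wrong. The sample size is an unadjusted two-proportion calculation and the main test matches it. Adjusted models are already prespecified, as secondary analyses. Which of two valid models is primary is partly a matter of preference. All of this stands, and it limits the point to efficiency.

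Further objections also carry weight:

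- **The gain is assumed.** No AUC is given, and an ideal normal score flatters a short list of coarse factors. The lower end of the range, near zero, is therefore a real possibility.
- **The change is not free.** The interim rule predicts the final P value. Its illustration uses raw counts per arm, and the 4.9% type I error was simulated from identical 5% risks, with no covariates mentioned. Both would need rechecking. The adjusted odds ratio is also conditional on the covariates, whereas the sample size and interim sections work with risks and risk ratios.
- **Completeness is not promised.** Only the risk indices are said to be calculated for each patient. The article does not say that every covariate will be complete.
- **The SAP may settle details.** Whether the main model includes hospital is something an SAP could add. Placing the risk factors in secondary analyses, however, is stated in the article.

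A reader might infer that the trial is underpowered without adjustment. The documents do not support this: power at the 4.5% criterion is 81.9% against a target of 80%, and the fall to 79.9% needs an assumed 5% of missing outcomes. A reader might also infer that the whole secondary list should move into the main model. It should not. Adherence to aseptic technique arises during surgery. The NNIS index is said to rest on some of the recorded variables, and duration of surgery is among these.

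**Conclusion.** The point holds as a modest efficiency improvement. On its natural reading the confirmatory model is unadjusted, while preoperative risk factors and the stratification factor are at hand. Prespecified adjustment would raise power from about 82% at P<4.5% by between almost nothing and about 3 points, and it did not raise the type I error in simulation. The size rests on an assumed AUC between about 0.60 and 0.80, the planned risks of 5% and 3.35%, and 2,500 analysed patients per arm. The unadjusted test remains valid and the sample size correct.

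**What to change.** Before unblinding, and so best before the interim analysis at 2,500 patients (2,101 were randomised when the article was written):

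1. Make the primary intention-to-treat model a logistic regression of SSI on treatment, hospital and a short fixed set of covariates known before randomisation, for example age, body mass index, diabetes, smoking, ASA score and surgical specialty. Take the primary P value from it.
2. Exclude intraoperative items, such as adherence to aseptic technique and any index component based on duration of surgery.
3. Prespecify a simple imputation for missing covariate values, so that no randomised patient is dropped for that reason.
4. Report the standardised risk ratio and risk difference beside the conditional odds ratio, and keep the unadjusted model as a sensitivity analysis.
5. Define the interim predictive probability for this same final test and repeat the simulation behind the 4.9% type I error.

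The expected AUC could be checked first in the sponsor's own cohort of 6,283 procedures, described under Current state of own research in the field, which was already analysed for SSI risk factors.

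The cost is protocol and SAP wording plus a repeat of the interim simulations. No new patients or data items are needed.

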### Study endpoints

The primary endpoint of this study is the occurrence of any SSI within 30 days after surgery (within one year after implant surgery). SSI are defined as incisional (either superficial or deep) infection or organ-space infection according to CDC criteria [1]. Superficial incisional SSI involve skin and subcutaneous tissues only, common stitch mini-abscesses are excluded; deep incisional infections involve fascia and muscle; and organ-space infections involve any organ or space other than the incised layer of body wall that was opened or manipulated during surgery.

The operating surgeon, his team and ward residents, and the patients are unaware of assignments to treatment groups and are therefore blinded for treatment allocation. The operating surgeon and his team perform routine wound surveillance according to clinical standards including diagnosis and treatment of SSI. The resident in charge of the patient on the ward is responsible for registration of SSI, cross-checked by the attending surgeon in charge. In addition, inpatients are seen regularly by members of the study team. This ensures appropriate sensitivity to detect in-hospital events. Clinicians are not allowed to overrule study team members in arbitrary situations about diagnosing of SSI.

For post-discharge follow-up, trained investigators blinded for treatment allocation contact all patients 30 days after surgery by telephone. The past or present occurrence of SSI is assessed using a standardized questionnaire, and the physician who performed post-discharge clinical follow-up is identified. Whenever ongoing SSI are suspected, patients are investigated in the outpatient clinic of the two involved study centers, clinically relevant microbiological samples are cultured as needed, and the patient receives standard treatment. Whenever the telephone assessment suggests past SSI, primary care physicians are contacted and outpatient charts reviewed to gain additional information for validation of the event as described below.

In case of implant surgery, an additional monitoring assessment is performed one year after surgery, covering the mandatory follow-up period of one year as defined by CDC [1].

To ensure appropriate specificity, all cases of SSI are validated by a board certified infectious disease specialist who is blinded for the intervention, based on a comprehensive review of patient history, clinical findings, microbiology results and follow-up data.

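### The secondary adjusted model calls all its covariates baseline, but adherence to aseptic technique is observed during the operation (minor)

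*Protocol article*

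**What the plan says.** The Statistical analyses section gives a logistic model with treatment group as the main exposure and states: "The main analysis will be an intention-to-treat analysis". For secondary analyses it then fixes a covariate list: "the logistic regression model will include the following known and suspected baseline risk factors for SSI: wound classification, ASA score, NNIS score, age", followed by "body mass index categories, presence of diabetes, smoking status, adherence to aseptic technique, and experience of the surgical team". The word baseline covers all nine items.

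Four other statements bear on this:

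- Randomization and intervention: "After written informed consent is obtained from eligible patients, they are randomized electronically and stratified by hospital". The antibiotic is then given before incision in both arms, and the anesthesiologist responsible for giving it is told the allocation.
- Patient and procedure characteristics lists what is collected. The list includes ASA score and also "wound class, type and duration of surgery, experience of the surgical team, surgical specialty, intraoperative core temperature, adherence to aseptic technique, and emergency procedure".
- The same section says of the SENIC-type and NNIS indices: "SSI risk indices are based on some of these variables and will be calculated for each patient". It does not say which variables.
- Study endpoints: "The operating surgeon, his team and ward residents, and the patients are unaware of assignments to treatment groups".

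**The concern.** A covariate measured before treatment cannot be changed by treatment, so adjusting for it leaves the randomized comparison intact. A covariate that arises afterwards has no such guarantee. If allocation shifts it and it is related to infection, the adjusted coefficient no longer estimates the full effect of allocation. If it also shares unmeasured causes with infection, bias of either sign can enter. Adherence to aseptic technique is in this position, yet the plan presents it as baseline.

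A second, weaker point concerns NNIS. A composite index entered beside items that it may be built from carries the same information twice. If it also uses duration of surgery, it is not known until the operation ends.

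At stake is the credibility of a prespecified adjusted estimate that readers will set beside the main result.

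**Working it through.** No figure in the protocol belongs to this point. The sample size of 5,000 uses no covariates and is not in question.

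**Step 1: order of events.** Consent, then randomization, then prophylaxis, then incision (Randomization and intervention). Aseptic technique is practised during the operation, and the article lists it next to intraoperative core temperature. It therefore follows both randomization and prophylaxis. This step needs nothing from outside the document.

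**Step 2: NNIS.** The model holds NNIS, ASA score and wound classification. The pool from which NNIS draws holds ASA score, wound class and duration of surgery, but the article says only that some of the pool is used. Overlap with two covariates, and dependence on duration, are probable but not proven.

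**Step 3: possible size (illustration only).** The document has no data on adherence, so every input here is an assumption except n = 5,000 in two equal arms. A simulation with 300 data sets per setting used a conditional odds ratio of 0.66, about 4% infections, and log odds ratios of 0.5 each for ASA, wound class and duration. Adherence had a log odds ratio of −0.5, and an unmeasured factor affected both adherence and infection. NNIS was taken as the sum of ASA, wound class and duration, each coded 0 or 1.

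*Overlap* (adherence not in the model):

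| Mean standard error | Without NNIS | With NNIS | Ratio |
|---|---|---|---|
| ASA | 0.155 | 0.225 | 1.45 |
| Wound class | 0.172 | 0.237 | 1.38 |
| Treatment | 0.157 | 0.158 | 1.01 |

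The ASA and wound-class coefficients fell from about 0.48 to near 0 (0.029 and 0.014). The duplication affects these terms and leaves the precision of the treatment estimate almost unchanged.

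*Adherence* (NNIS in both models): with allocation assumed to lower adherence by 0.5 on the logit scale in one arm, the mean treatment log odds ratio was −0.378 without adherence in the model and −0.392 with it.

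- Shift: 0.014. As odds ratios: exp(−0.378) = 0.685 and exp(−0.392) = 0.676.
- Simulation error of one mean: 0.156/√300 = 0.009. For a difference of two independent sets: 0.009 × √2 = 0.013. The shift is about 1.1 times this error, so the simulation alone does not resolve it.
- Rough check: with the unmeasured factor at zero, adherence is 1/(1 + exp(−1.5)) = 0.818 in one arm and 1/(1 + exp(−1.0)) = 0.731 in the other, a difference of 0.087. Multiplied by the fitted adherence coefficient of −0.255, the expected shift is about 0.022.

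A shift of 0.014 to 0.022 is 9% to 14% of the treatment standard error (0.014/0.157 and 0.022/0.157), even though a sizeable effect of allocation on adherence was assumed.

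**The case against.** The strongest reply is that nothing important depends on this list. The main analysis is by intention to treat, and the listed covariates enter only in secondary analyses. The surgeon and team are blinded, so allocation has little route to aseptic technique, and without such a route adjustment does no harm. The adjustment coefficients are not a stated target, so wide standard errors on ASA or wound class defeat no aim. All of this stands, and it limits the point to a minor one.

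It does not make the variable baseline. The anesthetic team knows the allocation, and in one arm it infuses in the operating room shortly before incision. That allocation has no effect on conduct there is a reasonable belief, but the design does not guarantee it. Nor can the point be left to a later analysis plan: the list is already fixed and labelled here, and a plan that copied it would carry the error forward.

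A reader might infer three stronger things that the document does not support:

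- That NNIS is certainly entered with its own components and fixed only after surgery. The components are not named.
- That wound class is also a post-randomization variable. The document never says that it is reassigned at surgery; under Inclusion criteria, wound class underlies the indication for prophylaxis and so eligibility.
- That the trial's main conclusion is at risk. It is not.

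**Conclusion.** The point holds in a narrow form. One of nine covariates described as baseline, adherence to aseptic technique, is observed during the operation, so adjusting for it is not baseline adjustment. Bias in the adjusted treatment effect would require that allocation changes adherence, which blinding of the surgical team makes unlikely. Its size cannot be derived from the document. The illustration, which rests wholly on assumed prevalences and effects, puts it at about 0.01 to 0.02 on the log odds scale.

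The NNIS part is conditional. If the index uses ASA score, wound class and duration of surgery, it duplicates two terms and depends on an intraoperative quantity. The duplication would then affect the covariate coefficients and not, to any material degree, the treatment estimate.

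Severity is minor. It would be too strong to say that the adjusted analysis loses the protection of randomization outright, since that depends on an effect of allocation for which the document gives no evidence.

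**What to change.** Four wording changes to the adjusted model:

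1. Restrict its covariates to variables fixed before prophylaxis, and add hospital. Hospital is the randomization stratification factor and is absent from the list.
2. Take adherence to aseptic technique out. Show it in a descriptive table by arm, or use it in a sensitivity analysis labelled as adjusting for an intraoperative variable.
3. Name the components of NNIS. Use either the index or its components, not both.
4. If NNIS uses duration of surgery, keep it out of the adjusted treatment model.

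The cost is text only, with no new data and no change to the sample size or main analysis. The downside is that one or two prognostic intraoperative variables are not used for adjustment.
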